## Abstract

**Background:**

Social anxiety disorder (SAD) is a highly prevalent mental disorder associated with enormous stress and suffering. Cognitive behavior therapy (CBT) is the first-line treatment for SAD, yet its accessibility is often constrained with long waiting times. Digital therapeutic applications, including psychoeducation and self-guided behavioral experiments in virtual reality (VR), could facilitate access and reduce waiting times. The study aims to investigate if ultra-short-time therapy involving self-guided digital therapeutic applications with VR components can reduce the severity of SAD.

**Methods:**

Forty SAD patients will participate in this randomized controlled trial. Half will get access to a self-guided, digital therapeutic application with exposure-based behavioral experiments in VR, while the other half will receive a control treatment. Both treatments include four therapeutic appointments. Changes in the severity of SAD will be measured after each appointment and on a 6-week follow-up assessment and will be compared between groups, with the change in SAD measured at baseline- and post-assessment as primary outcome.

**Discussion:**

Self-guided digital therapeutic applications including ultra-short-time therapy combined with VR could help reduce the waiting time for patients and relieve the health system. The results of this study may inform psychotherapists regarding the potential of self-guided digital therapeutic applications including exposure-based behavioral experiments in VR for SAD and will provide important insight for future research on VR therapy.

**Trial registration:**

Current Controlled Trials ISRCTN18013983. Registered on 1 February 2022.

## Background

Social anxiety disorder (SAD) is a highly prevalent disorder. With 12-month prevalences ranging between 1.5 and 7.1.% and lifetime prevalences between 2.5 and 12.1% [1], SAD is associated with a high load on the health system, enormous economic costs because of therapy and absenteeism [2], and a high impairment for affected individuals [1].

Social anxiety is characterized by the anxiety of being in the center of attention or of behaving embarrassingly. Thereby, blushing or trembling, fear of vomiting, and the urge of micturition or defecation are common symptoms [3]. These symptoms mainly appear in anxiety-inducing situations or when thinking about those situations and are associated with avoidance behavior, e.g., avoidance of social interactions or performing in front of others [4, 5]. When situations are not avoided, individuals engage in safety behavior (e.g., avoiding eye contact, wearing a scarf to hide symptoms of blushing, etc.) [6]. Safety behavior has three main problems: (1) individuals do not have correcting experiences about their expectations and worries, (2) symptoms of anxiety may increase, and (3) others might respond negatively [6]. Both experienced anxiety and avoidance cause individuals to experience significant impairment in everyday life [1].

Cognitive-behavioral therapy (CBT) is the first-line treatment for SAD [7]. Thereby, core therapeutic techniques are psychoeducation [8], exposure [9], and behavioral experiments [10]. During exposure-based behavioral experiments, patients are instructed to omit avoidance or safety behaviors and face the feared situation to test their pathogenic beliefs and to modify dysfunctional cognitive processes [7, 10].

Despite medium to large effect sizes of standard CBT for SAD [7], less than a quarter of individuals with SAD receive psychological or psychiatric treatment in high-income countries [1]. This has several reasons. First, a study by the Federal Chamber of Psychotherapists in Germany found an average waiting time of 20 weeks for psychotherapy [11]. Second, pre-treatment latencies contribute to pre-treatment attrition rates of up to 30.4% for individuals with SAD [12]. These numbers are worrisome, as untreated SAD mostly becomes chronic and spontaneous remissions seem to be the exception rather than the rule [13].

Technological advances in the field of e-health, like virtual reality and application-based health interventions, may help to overcome these problems. Application-based interventions including virtual reality exposure therapy have been shown to be effective in clinical settings [14]. For SAD, exposure-based VR therapy has been successfully applied [15–17]. VR therapy can include behavioral experiments (e.g., giving a presentation in front of a virtual audience to test out phobia-related expectations) [18]. It can reduce patients’ social anxiety and improve their quality of life [19]. Other advantages of exposure-based VR therapy are as follows: (1) relevant social situations can be simulated and are easier to implement [15], (2) simulations and their difficulty can be matched to the patient’s individual needs [20], and (3) it has higher acceptance and lower refusal rates than exposure in vivo [21]. For specific phobia and smoking, self-guided digital VR therapy has proven to be effective [14, 22, 23]. To access these benefits in SAD, application-based therapeutic interventions that may include psychoeducation and VR components to model feared situations can be used. These interventions can support ultra-short-time therapy, in which most of the therapeutic work will be provided within application. Even though application-based therapeutic interventions are a promising approach to reduce the enormous load on the health system, studies testing their efficacy are still sparse.

To extend the current knowledge and to test the efficacy of application-based short-term therapy including behavioral experiments in virtuo, one group of patients (experimental group) will get access to a digital (VR) application and four appointments with a psychotherapist, while the second group (control group) will get a control treatment composed of four appointments with a psychotherapist. We expect that patients who receive application-based treatment will show less symptoms of social anxiety at a post-assessment compared to a baseline assessment and at an interim, a post, and a 6-week follow-up assessment, compared to the control group. To test a clinically relevant change, the remission rates of patients between both groups will be compared at the follow-up assessment.

### Trial design

In the present randomized controlled trial, changes in SAD symptoms (post vs. baseline, interim vs. baseline, follow-up vs. baseline) will be compared between a group receiving the digital (VR) application and a control group in a superiority design. The study employs a 2 (condition: application-based vs. control treatment) × 4 (time: baseline assessment, interim assessment, post assessment, and 6-weeks-follow-up) design.

## Methods/design

### Participants

Patients with SAD will be recruited from the general population and routine care at the Outpatient Center for Psychotherapy of the University of Siegen, Germany. Participants will be recruited through newspaper reports, advertisements, and radio. Interested participants will be invited to take part in a telephone interview to access inclusion and exclusion criteria. Participants will be included if they fulfill the criteria for social anxiety disorder as a primary disorder. Criteria will be tested with a short diagnostic interview for mental disorders (Mini-Dips [24]). Participants must be at least 18 years old and not receiving therapy yet. Due to exposure-based behavioral experiments in virtual reality, participants who experienced a stroke or coronary disease in the past or are diagnosed with angina pectoris, cardiac arrhythmias, hypertension, asthma, or a chronic obstructive pulmonary disease, strong visual disorders or epilepsy or seizures in the past, or (possible) pregnancy will be excluded. Also, participants with psychological disorders with organic cause, vertigo, vestibular impairments, psychological or behavioral problems caused by psychoactive substances, schizophrenia, schizotypal or delusional disorders, severe depression or mania, acute suicidal tendencies, or lack of capability to negotiate a no-suicide agreement will be excluded.

### Sample size

In previous studies, medium to large effect sizes were found for exposure-based VR therapy when compared to a control treatment without behavioral exposure for self-report measures [25]. For self-guided therapy-derived interventions, small to medium effect sizes and a medium mean effect size were found for self-report measures [26]. Hence, we anticipate a medium effect size for the primary outcome of the present study. An a priori power analysis was conducted for the primary outcome (change in social anxiety symptoms as assessed by means of the Social Anxiety and Social Competence Deficits questionnaire; SASKO [27], measured at baseline- and post-assessment) using G*Power 3.1 [28] for a 2 × 4 repeated measures ANOVA (Cohen’s *d* = .50, *α* = .05, power = .80). The results indicated a required total sample size of 24 participants. Due to expected attrition, 40 participants will be included in the study, that is 20 per condition. Figure 1 shows a CONSORT flow diagram of the recruitment process.

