### Outcome measures

#### Primary outcome

The primary outcome measure will be the total score of the German version of the SASKO [27] measured at baseline assessment and post assessment (post-assessment–baseline assessment). The SASKO is a self-report questionnaire that contains the symptoms of SAD. It has four subscales: (1) anxiety of speaking and being in the center of attention (12 items), (2) fear of rejection (10 items), (3) interaction deficits (10 items), and (4) information processing deficits (8 items) and a total score (40 items). All items are judged on a 4-point Likert scale ranging from 0 (“never”) to 3 (“always/most of the time”). It has a high internal consistency (Cronbach’s *α* = .92) and good validity [27]. Participants will be presented with the SASKO at four time points. These time points are the baseline assessment (around 2 weeks after enrollment), interim assessment (6 weeks after baseline), post-assessment (10 weeks after baseline), and follow-up assessment (16 weeks after baseline).

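### The sample size of 24 is calculated for a 2 × 4 ANOVA and an effect about twice the stated d = 0.50, so the claimed 80% power does not apply to the baseline-to-post primary outcome

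*Protocol article*

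**What the plan says.** The Primary outcome section defines the outcome on two occasions: "The primary outcome measure will be the total score of the German version of the SASKO [27] measured at baseline assessment and post assessment", taken as post minus baseline. The Trial design section says that changes are compared between the two groups.

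The Sample size section gives the expected effect as follows: "Hence, we anticipate a medium effect size for the primary outcome of the present study". It ties the calculation to that outcome ("An a priori power analysis was conducted for the primary outcome"), but names the test as one "for a 2 × 4 repeated measures ANOVA" with inputs "Cohen’s *d* = .50, *α* = .05, power = .80". It then concludes: "The results indicated a required total sample size of 24 participants". The planned number is larger: "Due to expected attrition, 40 participants will be included in the study, that is 20 per condition". No attrition rate, correlation between measurements or sphericity correction is given. The section on data preparation and planned analyses says only that variance analytic methods will be used, with multiple imputation for intention-to-treat.

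**The concern.** The comparison called primary is a between-group difference in change over two occasions, with 1 numerator degree of freedom. The test that was sized covers four occasions and has 3. In addition, d describes a difference between two means, and halving it gives the right f only for a between-group difference in means. On a group-by-time term the same f stands for a much larger difference.

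This paragraph is the article's only justification for its sample size. Readers are told that 24 completers give 80% power for a medium effect. If that is not so, a non-significant result from a trial meant to inform psychotherapists could be taken as evidence that the application does not work, when the trial had little chance of detecting the effect it anticipated.

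**Working it through.** **Inputs from the article:** two groups, 1:1 allocation, d = 0.50, α = 0.05, power 0.80, four measurements in the sized test, two in the primary outcome, N = 24 required and 40 planned. **Assumed:** a two-sided test, and r and ε as shown at each step.

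**1. Reproduce 24.** For the within-between interaction with k groups and m measurements, with ε = 1:

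λ = N·m·f²/(1 − r), df1 = (k − 1)(m − 1), df2 = (N − k)(m − 1).

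Take f = 0.50/2 = 0.25, m = 4, r = 0.5.
- N = 24: λ = 24 × 4 × 0.0625/0.5 = 12, df 3 and 66, power 0.816.
- N = 22: power 0.775.

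So 24 is the smallest even N that reaches 0.80. Other tests with f = 0.25 or d = 0.50 do not give 24: the between-group main effect over four measurements needs 82, and a two-sided t test needs 128.

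**2. Use the two time points of the primary outcome.** Keep f = 0.25 and r = 0.5, with m = 2.
- N = 24: λ = 24 × 2 × 0.0625/0.5 = 6, df 1 and 22, power 0.649.
- 80% power needs N = 34 (power 0.807).

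**3. What f = 0.25 means on the interaction.** If the group difference at occasion j is δⱼ (in raw SDs), each cell's interaction effect is ±(δⱼ − mean δ)/2, so f² = mean[(δⱼ − mean δ)²]/4.
- Two occasions, differences (0, D): f = D/4, so f = 0.25 gives D = 1.0 raw SD. The SD of change is √(2(1 − r)) raw SDs, which is 1 at r = 0.5, so this is also 1.0 SD of change. For D = 0.50, f = 0.125.
- Four occasions (baseline, interim, post, follow-up):

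| Pattern of differences | Largest difference implied by f = 0.25 |
|---|---|
| 0, 0, D, D | 1.00 |
| 0, D, D, D | 1.15 |
| 0, D/2, D, D | 1.21 |
| 0, D/3, 2D/3, D | 1.34 (0.89 at post) |
| 0, D/2, D, D/2 | 1.41 |

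**4. Power of the primary contrast for d = 0.50 in raw SDs.** Two-sided noncentral t, with standardised effect 0.50/√(2(1 − r)) for a change score and 0.50/√(1 − r²) for baseline-adjusted ANCOVA.

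| r | Change, N = 40 | ANCOVA, N = 40 | Change, N = 24 | ANCOVA, N = 24 | N for 80%, change / ANCOVA |
|---|---|---|---|---|---|
| 0.3 | 26% | 37% | 17% | 23% | 178 / 118 |
| 0.5 | 34% | 43% | 22% | 27% | 128 / 98 |
| 0.7 | 51% | 58% | 33% | 38% | 78 / 68 |
| 0.8 | 68% | 73% | 46% | 50% | 54 / 48 |

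**5. Difference detectable with 80% power.**
- 20 per arm: 0.91 SD of change; with ANCOVA at r = 0.5, 0.91 × √0.75 = 0.79 raw SD.
- 12 per arm: 1.20 SD of change; with ANCOVA at r = 0.5, 1.20 × √0.75 = 1.04 raw SD.

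**The case against.** - **Unstated inputs.** A reader might infer that 24 proves r = 0.5 and ε = 1. It does not. The time main effect has the same λ and degrees of freedom when there are two groups, and pairs such as r = 0.6 with ε = 0.75, or r = 0.7 with ε = 0.5, also give 24. The values used above are likely software defaults and no more. The finding does not depend on them, because it holds across the range in step 4.
- **A single power figure.** A reader might infer that the trial simply has 34% power, or 22%, and would miss a medium effect two times in three. Those figures belong to an unadjusted two-sided change-score test at r = 0.5. The article's wording on analysis leaves room for ANCOVA, which at r = 0.7 would miss the effect 42% of the time. The 22% further requires that 16 of the 40 contribute nothing. The article gives no attrition rate and plans multiple imputation, so this is a worst case.
- **Arithmetic.** A reader might infer that the software calculation was wrong. It reproduces exactly; the fault lies in the choice of test and the conversion of the effect size.
- **The 2 × 4 test fits the declared design.** It does, and interim and follow-up comparisons are planned as well. But the article attaches the calculation to the baseline-to-post outcome. Nor would the omnibus test rescue the claim: with a largest difference of 0.5 SD and r = 0.5, its power at N = 40 is 23% to 43% across the patterns in step 3.
- **High correlation.** At N = 40 a change score reaches 80% at r of about 0.85, but power at N = 24 is then still only 57%.

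**Conclusion.** Wrong as written. The statement that 24 participants give 80% power at d = 0.50 does not hold for the primary outcome that it names. Changing only the number of time points raises the requirement from 24 to 34. Taking d = 0.50 as the difference in change raises it to 128 at r = 0.5 (98 with ANCOVA).

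With all 40 analysed, power for d = 0.50 is about 26% to 51% (change score) or 37% to 58% (ANCOVA) for r between 0.3 and 0.7, and remains below 80% at r = 0.8. With only 24 contributing, it is about 17% to 33% or 23% to 38%. These figures assume a two-sided 5% test, d in raw SD units and equal arms. The size of the shortfall depends on r, which the article does not give; its existence over r = 0.3 to 0.8 does not.

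**What to change.** Keep 40 participants and replace the power statement in the Sample size section and in the registry entry. The new text should:
- name the 1-df between-group comparison of baseline-to-post change as the test being powered;
- state that it has 80% power for a difference of about 0.9 SD of change if all 40 are analysed (about 0.8 raw SD with ANCOVA at r = 0.5), and about 1.2 SD if 24 remain (about 1.0 with ANCOVA);
- give the power for d = 0.50 as a range over stated values of r, and say whether the analysis adjusts for baseline;
- commit to interpreting the primary result by its 95% confidence interval, without reading non-significance as absence of effect.

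The cost is a less favourable power statement and some rewording. No extra patients are needed, and randomisation and outcomes are untouched.

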**Fig. 1 Fig1:**
[figure not shown]
The consort flow diagram. EG, experimental group; CG, control group; white, the same for both groups; grey, different for the groups

## Methods and materials

### Procedure

#### Screening

To pre-select the participants, a screening via telephone will be used, including SAD symptoms as outlined in the Mini-DIPS and inclusion and exclusion criteria. Participants that do not fulfill the criteria will be excluded and offered to be put on the waiting list of the Outpatient Center for Psychotherapy of the University of Siegen. The screening will be conducted by research assistants, trained by a psychotherapist. If participants fulfill the inclusion criteria, they will be invited to a first appointment with a certified psychotherapist.

#### First appointment (anamnesis)

During the first appointment with their psychotherapist (100 min), participants will receive information on the study and provide written informed consent. Further, patients’ motivation for seeking therapeutic help will be explored, and core symptoms and a biographical anamnesis will be obtained.

#### Second appointment (baseline assessment)

At a second appointment (around 100 min), a structured clinical interview, the Mini-DIPS, will be conducted by a psychotherapist to verify the diagnosis of SAD, to explore comorbid psychological disorders, and to test for psychological disorders leading to exclusion from this study. If eligible for participation, patients will be assigned to the experimental group (EG) or the control group (CG) according to a computer-generated randomization scheme and participate in an online survey, conducted by trained research assistants. Afterwards, patients randomized to the EG will receive their prescription for the application (Invirto 1.17.0, Sympatient, Hamburg; class I after the Medical Device Directive 93/42/EWG [29]). The EG will be asked to start the intervention, while the CG will be asked to wait until the next appointment.

#### Self-guided phase I

Participants in the EG will be provided with the prescribed therapeutic application [29] and the VR glasses to perform the behavioral experiments in virtuo. They will be instructed to complete the first units (Part 1: Psychoeducation and behavioral experiments in virtuo) within 6 weeks after the baseline assessment. Each unit is split into psychoeducation and exercises. Psychoeducation includes information on SAD and mechanisms involved in its development and maintenance (e.g., triggers, safety behavior, and dysfunctional cognitions). The exercises include relaxation exercises, behavioral analyses, and behavioral experiments in virtuo. The virtual elements can last up to 90 min: first, participants are familiarized with the virtual psychotherapist and the virtual reality experience. Afterwards, patients are confronted with two virtual anxiety-inducing contexts (a job application and a talk). These exercises are designed to train patients to identify safety behaviors (e.g., via video feedback), to test (and falsify) anxiety-inducing worries and distorted expectations, and to gain new experiences (e.g., anxiety with and without safety behaviors) with anxiety-inducing virtual situations. The CG will not receive a specific instruction for this phase.

#### Third appointment (interim assessment)

Six weeks after baseline assessment, that is after completion of part 1 (Psychoeducation and behavioral experiments in virtuo) for the EG, patients are invited to a third therapeutic appointment with a psychotherapist. During this appointment, patients in the EG will plan and practice the upcoming behavioral experiments in real social situations. To control for unspecific treatment effects in the EG that might be caused by contact with a psychotherapist, the CG will also meet a psychotherapist.

The CG will be informed on stress-reduction and relaxation techniques and the interim assessment will be filled in. The topic of stress and relaxation was chosen because it is not specific to the disorder. Afterwards, patients will fill in the questionnaires of the interim assessment (see Fig. 2).

**Fig. 2 Fig2:**
[figure not shown]
Schedule of enrollment, intervention, and assessment. Measurement schedule, including all outcome measures. An X in the corresponding box indicates that a measurement takes place at a certain time point. W, weeks after allocation; SASKO, Questionnaire for Social Anxiety and Social Competence Deficits; Mini-Dips, short diagnostic interview for mental disorders; ADS, Center for Epidemiological Studies Depression Scale; PMH, Positive Mental Health; URICA, University of Rhode Island Change Assessment Scale; FKK, Questionnaire on Beliefs in Competency and Control; ASI-3, Anxiety Sensitivity Index; STAI, State-Trait-Anxiety-Inventory

The interim assessment serves two purposes: first, it aims at assessing the effects of the psychoeducation and VR therapy (+ psychotherapist appointment) compared to the control treatment. Second, it allows for an investigation of add-on effects of the subsequent self-guided behavioral experiments in vivo.

#### Self-guided phase II

For the next 4 weeks, participants in the EG will be instructed to complete behavioral experiments in vivo while participants in the CG will be instructed to wait.

#### Fourth appointment (post assessment)

During the fourth appointment (around 100 min, 4 weeks after the interim assessment), patients of both groups will meet their psychotherapist to reflect on their experiences. Afterwards, the questionnaires of the post assessment will be filled in (see Fig. 2).

#### Follow-up assessment

At the follow-up appointment (6 weeks after the post assessment, around 100 min), both EG and CG will fill in the questionnaires, and a Mini-DIPS will be conducted by the psychotherapist to assess remission status. Afterwards, the CG will get the prescription for the application.

#### Participant retention

All participants can get feedback on their process from their therapists after the follow-up, and they will be reminded of appointments by the research assistants. At each appointment, therapists and research assistants will give verbal encouragement to complete application units to benefit most from the proposed treatment. To promote participant retention in the control group, participants will be given the prescription for the therapeutic application after the follow-up.

